### Sample size and non-inferiority margin

2.6

A sample size of 126 participants is needed to achieve a power of 0.80 to test the hypothesis that personalised multimodal physiotherapy is non-inferior to ACDF surgery, with a standard deviation of six points on the NDI, an alpha of 2.5%, and allowing for a drop-out rate of up to 20% [48,49].

To determine the non-inferiority margin, we calculated the Smallest Worthwhile Effect (SWE) for the Neck Disability Index (NDI). The SWE represents the minimum clinical benefit required to justify a treatment, accounting for its specific risks, costs, and burdens [50,51]. While a 20% between-group difference is typically recommended for conservative treatments [50], this threshold is often increased by 10% for chronic conditions [52].

In consultation with our patient representative, we set the SWE at 30%. Given that the Minimal Clinically Important Change (MCIC) for patients undergoing surgery for cervical radiculopathy is nine points on the NDI [53], the 30% threshold translates to 3 points non-inferiority margin. Consequently, physiotherapy is considered non-inferior to surgery if the difference in NDI improvement between the two groups is less than three points.

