#### Statistical analysis

2.9.1

First, normality of the data will be checked by the Kolmogorov-Smirnov test and visual inspection of Q-Q plots, box plots, and histograms. If needed, data will be transformed to obtain normal residuals. The primary analysis will be conducted according to the intention-to-treat principle, with secondary analyses performed based on the per-protocol approach. A one-sided alpha of 2.5% will be used. For the primary and secondary outcomes, linear mixed models will assess between-group differences in outcome measures over 12 months. To analyse the over-time effect, the fixed part of the model will include the outcome measure over time, treatment group, and baseline outcome correction (when applicable). A random intercept will be selected to account for the correlated nature of multiple measurements from the same participant. Potential confounders will be included as covariates in the adjusted model. To assess the differences in treatment effect at each time point, we will include an interaction term between time and treatment group. The regression coefficient (B), p-value, and confidence intervals (95% CI) will be computed for the crude models (only corrected for the baseline value of the outcome) and the confounder-adjusted models.

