#### Non-inferiority evaluation

2.9.2

Differences between the study-arms with 95% confidence interval and p-values will be calculated for the crude and adjusted models based on potential differences in patient characteristics with a non-inferiority margin of three points on the NDI over 12 months. Missing data and reasons for drop-outs will be reported. Linear/logistic mixed models handle missing data more flexibly due to its reliance on maximum likelihood estimation, which allows for the incorporation of missing values under missing at random assumptions.

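### The written non-inferiority criterion names neither a confidence limit nor a direction, so it permits a point-estimate rule that does not fit the stated alpha and power

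*Protocol article*

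**What the plan says.** Section 2.6 of the protocol article (Sample size and non-inferiority margin) derives the margin, saying that "the 30% threshold translates to 3 points non-inferiority margin". It then gives the only sentence in the document on when success is declared: "physiotherapy is considered non-inferior to surgery if the difference in NDI improvement between the two groups is less than three points". The same section ties the sample size to a hypothesis test: "A sample size of 126 participants is needed to achieve a power of 0.80 to test the hypothesis". The inputs are an SD of 6 NDI points and an alpha of 2.5%, with up to 20% drop-out.

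Section 2.9.1 (Statistical analysis) adds "A one-sided alpha of 2.5% will be used" and plans a regression coefficient, a p-value and a 95% confidence interval for the crude and the adjusted models. It does not say which null value the p-value refers to.

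Section 2.9.2 (Non-inferiority evaluation) says: "Differences between the study-arms with 95% confidence interval and p-values will be calculated for the crude and adjusted models". The same sentence ends "with a non-inferiority margin of three points on the NDI over 12 months". It lists the ingredients of the decision without stating the decision.

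**The concern.** A non-inferiority conclusion normally rests on a confidence limit lying on the right side of the margin. The article's one criterion refers only to the difference being under three points.

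Two things are left open:

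- **Estimate or limit.** The sentence can be applied to the estimated difference. An estimate of 2 points in favour of surgery would then pass, although its confidence interval reaches well beyond the margin.
- **Direction.** The quantity is a difference in improvement, where more is better. Read as physiotherapy minus surgery, the value is below three however much worse physiotherapy does. Read as an absolute difference, physiotherapy that is better by more than three points would fail. Only surgery improvement minus physiotherapy improvement gives a sensible rule, and the text does not say that this is meant.

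At stake is the trial's main conclusion: whether physiotherapy can stand in for surgery in patients who have a surgical indication.

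**Working it through.** **Inputs.** From section 2.6: margin 3, SD 6, alpha 2.5%, power 0.80, 126 participants, drop-out up to 20%. From section 2.9.1: the alpha is one-sided. From section 2.3.2: allocation is 1:1, so 63 per arm. Assumption: the true difference used for power is 0. The article gives no number but speaks of assumed comparable effectiveness. All results use the normal approximation for a simple two-group comparison.

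**Step 1: which rule does the sample size correspond to?** For a test against the margin, n per arm = 2 × [SD × (1.960 + 0.842) / margin]² = 2 × [6 × 2.802 / 3]² = 62.8, rounded up to 63, or 126 in total. The stated number is therefore reproduced by a confidence-limit test at one-sided 2.5%, but only before drop-out. Allowing for 20% drop-out, the same inputs give 126 / 0.8 = 157.5, so 158; that is a separate matter. Because of it, results are shown for 63 per arm and for 50 per arm (126 × 0.8 = 100.8 in total).

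**Step 2: standard error.** SE = 6 × √(2/n), which is 1.069 for n = 63 and 1.200 for n = 50.

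**Step 3: compare the two rules.** Let d be the true difference, positive when physiotherapy is worse.

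- Point-estimate rule: P(pass) = Φ((3 − d) / SE)
- Confidence-limit rule: P(pass) = Φ((3 − d) / SE − 1.96)

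| True d | Estimate rule, 63 per arm | Estimate rule, 50 per arm | Limit rule, 63 per arm | Limit rule, 50 per arm |
|---|---|---|---|---|
| 0 | 99.7% | 99.4% | 80.1% | 70.5% |
| 3 | 50% | 50% | 2.5% | 2.5% |
| 4 | 17% | 20% | 0.2% | 0.3% |

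Example for d = 4 and 63 per arm: (3 − 4) / 1.069 = −0.935, so Φ(−0.935) = 17%. With the limit rule, Φ(−0.935 − 1.96) = Φ(−2.895) = 0.2%.

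**Step 4: the largest estimate that passes the limit rule.** 3 − 1.96 × SE gives 3 − 2.095 = 0.90 with 63 per arm, and 3 − 2.352 = 0.65 with 50 per arm. An estimate of 2 points with 63 per arm has an upper limit of 2 + 2.095 = 4.10. It satisfies the sentence in section 2.6 if that is applied to the estimate, and fails the limit rule.

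**The case against.** The strongest reply is that the protocol does not adopt a point-estimate rule at all. The sentence speaks of the difference and never says observed or estimated. It closes the derivation of the margin, so it can be read as defining non-inferiority for the true difference. A one-sided 2.5% alpha corresponds exactly to one limit of a two-sided 95% interval. Section 2.9.2 puts the difference, its interval, the p-values and the margin in one sentence. The sample size matches the limit rule before drop-out, whereas an estimate rule would leave the stated alpha and power without a function. The document is also a condensed article, and formal hypotheses are often left to the full protocol or the analysis plan.

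Most of this stands as evidence of intent. A reader might infer that the trial will declare non-inferiority half the time at the margin; the documents do not support that. The 50% belongs to any point-estimate rule whatever the sample size or SD, so it describes one reading of the sentence and is not an operating characteristic of this trial. A reader might also infer that the planned p-value tests a difference of zero and that a non-significant result would be taken as non-inferiority. No passage says either.

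What the reply does not remove is that the article does not defer the criterion: it states one, and applied to the estimate that criterion conflicts with the document's own alpha and power. The missing direction also remains if the sentence is read as being about the true difference.

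**Conclusion.** The point holds as a defect in a stated rule. The only success criterion omits the confidence limit and the direction, and the section on non-inferiority evaluation does not supply them. The rest of the design suggests that a confidence-limit test is intended, so there is no evidence that the wrong rule will be applied, but the sentence as written permits it.

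The permitted rule differs greatly from the likely intended one: at the margin its error is twenty times the stated alpha, and it would accept estimates up to 3 points where the limit rule stops at 0.90 or lower. The figures other than the 50% rest on the SD of 6 and a simple two-group comparison. Repeated measures or baseline adjustment could shrink the standard error and raise the 0.90 and 0.65 thresholds somewhat; the article gives no figure for this.

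**What to change.** In section 2.6 replace the criterion, and repeat it in section 2.9.2, with wording such as:

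*Non-inferiority is concluded only if the upper limit of the two-sided 95% confidence interval for the baseline-adjusted mean NDI difference over 12 months (physiotherapy minus surgery, higher = worse; equivalently, surgery improvement minus physiotherapy improvement) lies below the non-inferiority margin. Any p-value given for non-inferiority is one-sided and tests the null hypothesis that this difference is at least as large as the margin.*

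The cost is this wording in two sections, with no extra data. The article expects data collection to finish by July 2027, with analysis to follow, so the change can be made and dated before any outcome is analysed.

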### Economical evaluation

2.7

The economic evaluation will be performed from a societal and healthcare perspective, according to the Dutch Guideline for Economic Evaluations [54]. Societal costs will include all costs related to the interventions under study irrespective of who pays or benefits, such as the cost of the prescribed treatment, other healthcare use, informal care, and paid and unpaid productivity losses (including both absenteeism and presenteeism). Healthcare costs only include costs accruing to the standard Dutch healthcare sector. Treatment costs will be micro-costed. All other costs will be measured via cost questionnaires, and valued using the Dutch manual for costing studies in healthcare [55]. The EQ-5D-5L health states will be converted into utility scores using the Dutch tariff for the EQ-5D-5L [56]. Quality-adjusted Life Years (QALYs) will be estimated via the ‘Area under the Curve’ approach.

### Process evaluation

2.8

A process evaluation of the delivery of the personalised multimodal physiotherapy will be conducted in accordance with the UK MRC guidelines on both patient and therapist level [57]. Several research objectives have been formulated using the mechanisms of treatment and are identified in a logic model. These include contextual barriers and facilitating factors for implementing the treatment (i.e., reach of the target population and delivery of the treatment by investigating dose delivered/received and fidelity) and mechanisms of impact (i.e., did the treatment work as intended). We will contact participants and physiotherapists by email to inquire whether they would like to participate in the focus groups and/or (semi-structured) interviews. To collect data, several questions regarding treatment satisfaction at three months follow-up, (semi-structured) interviews and focus groups will be conducted with physiotherapists and patients from both interventions. Also, field notes and routinely collected data will be used for the process evaluation. All data will be collected during or shortly after the study. A written standard operating procedure will be used to ensure consistency and quality during data collection.

### Analyses

2.9

#### Statistical analysis

2.9.1

First, normality of the data will be checked by the Kolmogorov-Smirnov test and visual inspection of Q-Q plots, box plots, and histograms. If needed, data will be transformed to obtain normal residuals. The primary analysis will be conducted according to the intention-to-treat principle, with secondary analyses performed based on the per-protocol approach. A one-sided alpha of 2.5% will be used. For the primary and secondary outcomes, linear mixed models will assess between-group differences in outcome measures over 12 months. To analyse the over-time effect, the fixed part of the model will include the outcome measure over time, treatment group, and baseline outcome correction (when applicable). A random intercept will be selected to account for the correlated nature of multiple measurements from the same participant. Potential confounders will be included as covariates in the adjusted model. To assess the differences in treatment effect at each time point, we will include an interaction term between time and treatment group. The regression coefficient (B), p-value, and confidence intervals (95% CI) will be computed for the crude models (only corrected for the baseline value of the outcome) and the confounder-adjusted models.

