#### Primary outcomes

2.5.1

The primary outcome is disability over 12 months, measured with the Neck Disability Index (NDI) [39], which assesses self-reported pain intensity and limitations of activities in daily life. The Dutch version of the NDI is a valid and responsive measure of disability [40].

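### The normality rule lets the primary NDI be transformed, but the non-inferiority margin exists only in raw NDI points

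*Protocol article*

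**What the plan says.** Section 2.9.1 (Statistical analysis) begins with a distributional check: "First, normality of the data will be checked by the Kolmogorov-Smirnov test and visual inspection of Q-Q plots, box plots, and histograms". The next sentence gives the consequence: "If needed, data will be transformed to obtain normal residuals". No transformation is named. The same paragraph then sets out the models: "For the primary and secondary outcomes, linear mixed models will assess between-group differences in outcome measures over 12 months". The NDI is the primary outcome (section 2.5.1), so the check and the possible transformation apply to it. The paragraph ends by reporting the regression coefficient B with a p-value and 95% confidence interval.

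The decision rule is in raw points wherever it appears. Section 2.6 derives it ("the 30% threshold translates to 3 points non-inferiority margin") and applies it: "physiotherapy is considered non-inferior to surgery if the difference in NDI improvement between the two groups is less than three points". Section 2.9.2 repeats it for the analysis: "with a non-inferiority margin of three points on the NDI over 12 months". The Discussion restates 3 points on the NDI. The standard deviation of six in section 2.6 is on the same scale. The article gives no margin on another scale and no method for returning a transformed result to NDI points.

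**The concern.** A non-inferiority conclusion compares a confidence limit with a fixed margin, so both must be on the same scale. A non-linear transformation moves the coefficient to another scale: a log gives a ratio, and a square root gives a difference of roots. On such a scale, 3 points has no single value, because its size depends on the NDI level at which it is evaluated. If the check led to a transformation, the analyst would have to choose a conversion of the margin or a back-transformation of the estimate, with the data already in view. The primary conclusion would then rest on a step that was not pre-specified.

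The check is also loosely aimed. It looks at the distribution of the data, while its stated purpose is normal residuals. A bounded score can look non-normal while the estimated mean difference is well behaved at this sample size.

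**Working it through.** **1. The plan's own figures are in raw points.** Section 2.6 takes 30% of a 9-point minimal clinically important change: 0.30 × 9 = 2.7, stated as 3 points. With margin 3, SD 6, one-sided alpha 2.5%, power 0.80 and no true difference, n per arm = 2 × (1.960 + 0.842)² × 6² / 3² = 62.8, so 63 per arm and 126 in total. That is the stated number before any drop-out is added. How the 20% allowance fits is a separate question and does not bear on this point. The margin, SD and sample size all assume the raw scale.

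**2. What 3 points becomes after transformation.** The surgery-arm mean μ and both transformations are assumptions.

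- log(NDI+1): ln[(μ+4)/(μ+1)]. At μ = 5, ln(9/6) = 0.405; at 10, ln(14/11) = 0.241; at 20, ln(24/21) = 0.134.
- Square root: √(μ+3) − √μ. At μ = 5, 0.592; at 10, 0.443; at 20, 0.324.

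**3. The reverse mapping.** Fix the log(NDI+1) margin at its value for μ = 10, a ratio of 14/11. In points it then allows (μ+1) × (14/11 − 1): 6 × 0.2727 = 1.64 at μ = 5, 3.00 at μ = 10, and 21 × 0.2727 = 5.73 at μ = 20.

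**4. Effect on the test.** The mapping in steps 2 and 3 treats single values, whereas a log-scale model compares means of logs, so a simulation was run. It assumed gamma-distributed NDI, surgery mean 10, SD 6 in both arms, 63 per arm, one time point and 40,000 runs. The upper 97.5% limit was compared with the margin. Type I error is at a true 3-point deficit and power is at equality.

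| Analysis | Type I error | Power |
|---|---|---|
| Raw NDI, margin 3 | 0.023 | 0.80 |
| log(NDI+1), margin converted at mean 5 | 0.229 | 0.98 |
| log(NDI+1), margin converted at mean 10 | 0.005 | 0.67 |
| log(NDI+1), margin converted at mean 20 | <0.001 | 0.26 |

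The nominal type I error is 0.025. The reference mean used for the conversion can therefore decide the result. Even at the true mean of 10 the error rate moves well below nominal, because the log analysis tests a different quantity.

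**5. Is transformation needed for validity?** On these skewed data the raw-scale test kept its type I error at 0.023 to 0.024 with surgery means of 8 or 10 and with 63 or 50 per arm (50 is roughly what remains after 20% drop-out). With the physiotherapy SD raised to 7.8 it was 0.027 to 0.028. Under these assumptions the raw-scale test is adequate.

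**The case against.** The strongest reply has five parts.

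- **The trigger is not automatic.** The Kolmogorov-Smirnov test is combined with plots, the aim is normal residuals, and the action follows only if needed. This stands. A reader might infer that a bounded, skewed score is likely to set the rule off. The documents do not support that, because they give no NDI mean, skewness or floor proportion. In simulated rounded gamma scores (SD 6, n = 100, means 10 to 20) the test rejected in anything from about 6% to about 98% of runs, depending on the mean and on whether the Lilliefors correction was used. That range shows only that the answer is unknown.

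- **Transformation need not leave the question open.** A reader might infer that non-inferiority would become undecidable, or could be decided only with a post hoc margin. That goes too far. A transformed model can be back-transformed to a mean difference in NDI points, by the delta method or a bootstrap, and compared with the original 3 points. What remains is that the article does not provide this route, and adopting it after seeing the data would also be post hoc.

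- **The specific section may govern the general one.** Section 2.9.2 is the dedicated non-inferiority section and speaks in points, so it could be read as keeping the NDI raw. That is a reasonable reading, but the article does not say so, and section 2.9.1 names the primary outcome expressly.

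- **The figures are illustrative.** The transformation, means and gamma shape are all assumed. The most adverse result (0.229) needs a margin anchored at 5 when the true mean is 10. This stands, and the numbers should be read as showing sensitivity, not as a forecast.

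- **A statistical analysis plan may settle it.** It may. The objection here is to a stated rule that does not fit the stated margin, and such a plan would have to override or supplement that sentence.

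**Conclusion.** The point holds in a conditional form. As written, the article allows the primary NDI to be transformed after inspection of the data, and it defines non-inferiority only in raw NDI points. If both rules were followed and a transformation were made, the reported B and interval could not be set directly against the 3-point margin, and the bridging step would be chosen with the data in view. The illustrative size is 0.41, 0.24 or 0.13 on log(NDI+1) for the same 3 points at assumed surgery means of 5, 10 and 20. The arithmetic is exact, but the means and the transformation are assumptions. Whether the rule would come into play cannot be told from the document. The sentence should be corrected before analysis, because the effect could be decisive if it applied.

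**What to change.** Add to section 2.9.1, and carry into the statistical analysis plan, wording such as: *The primary non-inferiority analysis of the NDI is done on the original scale whatever its distribution. If model residuals are clearly non-normal, the 95% confidence interval is obtained from robust standard errors or a participant-level bootstrap, and its limit is compared with the 3-point margin. Any analysis of a transformed NDI is a sensitivity analysis only.*

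Replace the Kolmogorov-Smirnov test on the raw data with an assessment of model residuals. The margin and the sample-size inputs do not change. The cost is a sentence or two of text and negligible extra analysis work.

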##### Participating physiotherapists

2.4.1.1

Physiotherapists who hold a master's degree in musculoskeletal physiotherapy are eligible to deliver the physiotherapy treatment. During a one-day training, working mechanisms of interventions are explained, techniques are practiced, case-based training is provided to enhance practical decision-making skills and a manual is distributed describing relevant theory. Due to the personalised nature of the treatment, physiotherapists use their clinical expertise to determine the appropriate frequency and duration, rather than following a fixed schedule and personalise interventions within protocol guidelines. A guideline for therapy intensity is the resolution of treatment-related pain and/or symptom exacerbation within 24-36 h. Physiotherapists are instructed to monitor each individual treatment session and document the details of the interventions provided. Quality assurance is maintained through regular communication with physiotherapists and evaluation of their adherence to the protocol. Additionally, physiotherapists can seek expert guidance from two professionals of the research team ([name]) who have over ten years of relevant experience.

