#### Cost-effectiveness analyses

2.9.3

The economic evaluations will be performed for the primary effect measure ‘disability’ and QALYs. The Incremental Cost-Effectiveness Ratio (ICER) will be calculated by dividing the difference in costs across study arms by the corresponding difference in effects. These differences will be estimated using regression techniques that will account for one or more of the following statistical challenges: baseline imbalances, skewed costs and/or effects, correlated costs and effects, clustering of data and missing data, if applicable [58]. Incremental cost-effect pairs will be plotted on cost-effectiveness planes, and cost-effectiveness acceptability curves will be constructed. The latter indicate the probability of personalised multimodal physiotherapy being cost-effective in comparison to surgery for various values of willingness to pay (i.e., the maximum amount that decision-makers are willing to pay per unit of effect gained). Sensitivity analyses will be performed to assess the robustness of the results (e.g., complete-case analysis and per protocol).

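### The primary NDI model has a random intercept for participant only; if outcomes vary by physiotherapist or surgeon, the interval that decides non-inferiority is too narrow, by an amount the protocol does not determine

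*Protocol article*

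**What the plan says.** Section 2.9.1 (Statistical analysis) sets out both parts of the clinical model. The fixed part has time, treatment group and the baseline value. The random part is: "A random intercept will be selected to account for the correlated nature of multiple measurements from the same participant". An adjusted model adds potential confounders, which section 2.9.2 (Non-inferiority evaluation) describes as patient characteristics. Section 2.9.2 then compares the 95% interval with the three-point margin. Neither section has a term for physiotherapist, surgeon or hospital.

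On delivery, section 2.4.1 places physiotherapy in individual sessions at the therapists' own practices, and section 2.4.1.1 says "physiotherapists use their clinical expertise to determine the appropriate frequency and duration, rather than following a fixed schedule". Section 2.4.2 has surgery done by neurosurgeons in several hospitals, with cage, plate and side of approach partly left to the surgeon.

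The economic analysis (section 2.9.3) lists the issues its regressions may handle: "baseline imbalances, skewed costs and/or effects, correlated costs and effects, clustering of data and missing data, if applicable". That analysis covers disability as well as QALYs.

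Section 2.6 says "A sample size of 126 participants is needed to achieve a power of 0.80", "with a standard deviation of six points on the NDI", and mentions no design effect.

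**The concern.** Two patients of the same physiotherapist share that therapist's skill and choices; two patients of the same surgeon share that surgeon's technique. Because each provider normally works in one arm only, provider effects do not cancel in the comparison of arms. They add variance to each arm mean that a participant intercept cannot capture.

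The direction matters. In a superiority trial a standard error that is too small produces false differences. Here it pulls the upper confidence limit below the margin too often, so physiotherapy would be declared non-inferior more often than the planned error rate allows.

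A secondary point concerns the same sentence. A participant intercept alone imposes equal variances and equal correlations at 3, 6 and 12 months. Section 2.9.1 also plans a time-by-group interaction to give differences at each visit, and those standard errors depend on this assumption.

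**Working it through.** **Inputs from the protocol.** 126 randomised 1:1 (63 per arm); SD 6; margin 3; "A one-sided alpha of 2.5% will be used"; dropout up to 20%; NDI follow-up at 3, 6 and 12 months.

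**Inputs not in the protocol (assumptions).** Provider ICC 0.02 to 0.10; patients per provider m = 2 to 8. With 63 per arm this means about 63/8 ≈ 8 to 63/2 ≈ 32 providers per arm.

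**Step 1: the plan's own figure.** Per arm, n = 2 × 6² × (1.960 + 0.842)² / 3² = 62.8, so 63 per arm and 126 in total. The stated total is thus obtained with a design effect of exactly 1. (It is also obtained before any dropout allowance; 63/0.8 gives 79 per arm, or 158. That is a separate issue and no part of this point.)

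**Step 2: effect of ignoring provider.** Design effect DE = 1 + (m − 1) × ICC. The correct interval is wider than the planned one by a factor √DE if both arms are clustered, or √((1 + DE)/2) if one is. The true one-sided error at the margin is 1 − Φ(1.96 / factor).

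| m | ICC | DE | Error, one arm clustered | Error, both arms clustered |
|---|---|---|---|---|
| 2 | 0.02 | 1.02 | 0.0256 | 0.0262 |
| 2 | 0.05 | 1.05 | 0.0264 | 0.0279 |
| 6 | 0.05 | 1.25 | 0.0323 | 0.0398 |
| 8 | 0.02 | 1.14 | 0.0291 | 0.0332 |
| 8 | 0.10 | 1.70 | 0.0458 | 0.0664 |

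**Step 3: one illustrative case.** Take 63 × 0.8 = 50.4 completers per arm and assume 11 providers per arm (m ≈ 4.6) with ICC 0.05. DE = 1.18, the interval should be 8.6% wider, and the error is 0.0355 with both arms clustered (0.030 with the physiotherapy arm only). An interval of the correct width has power 0.64, against 0.71 at the same dropout without clustering. With 30 providers per arm at the same ICC, the interval should be only 1.7% wider; with 5, it should be 21% wider.

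**Step 4: check by simulation.** With 50 per arm, three visits, within-patient correlation 0.6 and a per-visit ICC of 0.05 in both arms, the planned analysis gave errors of 0.064, 0.045, 0.040 and 0.032 for 5, 8, 11 and 20 providers per arm, and about 0.025 at ICC 0. The formula gives 0.052, 0.041, 0.0355 and 0.029. The simulated values are higher chiefly because a per-visit ICC of 0.05 becomes 0.05 / ((1 + 2 × 0.6)/3) = 0.068 for a patient's mean over three visits.

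**Step 5: visit covariance.** If the SD at 12 months were 7 (an assumption) and the pooled SD 6, the random-intercept standard error at that visit would be 1 − 6/7 = 14% too small, with error 1 − Φ(1.96 × 6/7) = 4.6%. For the average over 12 months the picture differs. A simulation with SDs of 5, 6 and 7, correlations 0.7/0.4/0.7, 50 per arm and 1,500 runs gave 0.030 with complete data and 0.026 with 20% dropout (Monte Carlo error about 0.004), close to nominal.

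**The case against.** The best counter-argument is that the size is unknown and may be trivial. That stands. Therapists work in their own practices, and one to three patients each is as compatible with the text as eight. At two per provider and ICC 0.02 to 0.05, the error is only 2.6% to 2.8%.

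It can also be said that naming a participant intercept does not exclude further levels, and that an analysis plan not shown here may add them. That is possible. But the article states the random part and its purpose rather than leaving it open, and an analysis plan that followed it literally would carry the gap over.

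Three stronger readings are tempting, and the protocol does not support them:

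- **That the 11 hospitals and clinics show the clustering.** Section 2.3.1 describes them as the sites where neurologists inform patients, before randomisation. Site effects common to both arms do not narrow the interval in this way; only provider effects within an arm do.
- **That section 2.9.3 contradicts section 2.9.1.** Its mention of clustering is one item in a conditional list. It shows that clustering was thought of for the same outcome, not that the clinical model is inconsistent with it.
- **That the random-intercept covariance undermines the non-inferiority decision.** The decision rests on the NDI over 12 months, for which step 5 shows little effect.

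**Conclusion.** The point holds in direction and not in any fixed size. With a positive provider ICC and more than one participant per provider, the planned interval is too narrow, and the error favours declaring non-inferiority. Under the assumed ranges (ICC 0.02 to 0.10, 2 to 8 patients per provider), the one-sided error is about 2.6% to 4.6% with one arm clustered and 2.6% to 6.6% with both. A reader might infer that the error rate is known to be well above 2.5%. The protocol does not support that, because it gives neither ICC nor provider numbers, and the inflation almost vanishes when patients are spread thinly. The covariance point is secondary and limited to the visit-specific contrasts. The change is worth making because it is cheap and can be fixed before the analysis, which the article expects to begin around July 2027.

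**What to change.** 1. Record the treating provider for every participant, and add to the primary NDI model a provider-level random intercept with a separate variance in each arm. Use small-sample degrees of freedom (Kenward-Roger or Satterthwaite).
2. If that model does not converge, use provider-clustered standard errors with a small-sample correction and a t reference. Clustered errors with normal critical values are not enough. In simulation at ICC 0.05, with about 50 per arm, they still gave 5.1%, 3.8% and 3.6% for 5, 8 and 11 providers per arm; a small-sample t reference gave 2.4% to 2.6% for 5 to 20.
3. State how provider is assigned under intention-to-treat. Section 2.4.3 allows delayed surgery after physiotherapy and cancelled surgery, so some participants will have two providers or none.
4. Treat clustering the same way in the clinical and economic analyses.
5. Secondarily, use an unstructured covariance over the 3, 6 and 12 month visits (six parameters) so that the visit-specific differences have correct standard errors.

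The cost is revised wording, one recorded item and a slightly wider interval. Physiotherapists already document each session (section 2.4.1.1), so provider identity should be obtainable. Provider codes should be masked, because section 2.3.2 has the statistician blinded.
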